# Effectiveness of a universal classroom-based preventive intervention (PAX GBG): A research protocol for a matched-pair cluster-randomized controlled trial

**DOI:** 10.1016/j.conctc.2017.08.013

**Published:** 2017-08-30

**Keywords:** Mental health, Intervention, Children, Good behavior game, Prevention, Health promotion

## Abstract

**Introduction:**

The PAX Good Behavior Game (PAX GBG) is a universal classroom-based program that promotes children's mental health. In Estonia, the intervention is delivered to first grade students (aged seven to eight) within the regular school curriculum. The current work describes a protocol for a cluster-randomized controlled trial (RCT) of the PAX GBG conducted in Estonia.

**Design and methods:**

This is an ongoing, pragmatic, two-year, matched-pair, cluster-RCT conducted in Estonian elementary schools. Schools were matched to pairs based on their geographical location and number of students per classroom. One school in each pair was randomly selected to receive the intervention and the other placed on a wait-list as a control. 42 schools provided baseline data during the autumn of 2016. Data is collected at two more points in time – seven months and 19 months post-baseline. Outcomes of children's mental health and behavior are measured by the teacher- and parent-rated Strengths and Difficulties Questionnaire, parent-rated Swanson, Nolan, and Pelham – IV Questionnaire and the Go/No-Go task completed by children. Teachers also rate their self-efficacy and overall classroom behavior.

**Discussion:**

This study aims to test the effectiveness of the intervention in Estonian classrooms with a newer version of the rigorously tested GBG program. To our knowledge, this study is the first to measure the effects of the intervention on children's inhibitory control, which has been associated with externalizing problems in the literature. The results from this trial will provide further understanding into how the program influences children's well-being and self-control.

**Trial registration:**

ClinicalTrials.gov registry (NCT02865603).

## Introduction

1

Children have the right to live and grow up in an environment that provides the best possible conditions for their health [1]. A child's mental health and well-being arise through interactions between individual, social and environmental factors that shape their behavior and choices [2]. Psychological well-being, personal and social competence, strong attachment to parents and a supportive school environment are all powerful factors that contribute to children being less vulnerable to drug use, mental health problems, dropping out of school, delinquency, violence and risky sexual behavior [3].

School is a frequently used setting for preventive interventions targeting children [4] as they spend large amounts of their time there. Several universal school-based prevention programs have demonstrably reduced psychological and behavioral problems in children [5]. One of these is the Good Behavior Game (GBG), a behavior management strategy that has been used for more than 40 years [6]. The GBG addresses disruptive and aggressive behavior during middle childhood, important behavioral antecedents of adolescent drug use and mental health problems [7].

The goal of the GBG is to increase children's self-regulation and peer-cooperation [5]. Interventions addressing self-control during childhood can prevent a range of difficulties, for example, substance dependence and criminal offences during adulthood [8]. At the same time, cooperative social environments foster children's successful development and promote their mental health [9].

Several studies across the United States, the Netherlands and Belgium have attested the effectiveness of GBG and found that the GBG reduces behavioral and emotional problems [10], [11], [12], [13], [14], [15], [16], prevents the use of tobacco, alcohol and illicit drugs [7], [17], [18], [19] and improves educational attainment [7], [20]. Although, in general, the program has proven to be effective, one study also determined that the intervention did not have a positive impact on children from dysfunctional families or those with combinations of behavioral and social risks [21].

The PAX version of the GBG (PAX GBG, developed by the Paxis Institute in the United States) was implemented in Estonia for the first time in 2014 by the Estonian National Institute for Health Development (NIHD). In addition to the original classroom-based game where students are reinforced for their mutual success in withholding inappropriate behavior, PAX GBG includes evidence-based kernels or behavior influence strategies [22]. There are four categories of kernels based on their effect: antecedent, relational, physiological and reinforcement. These kernels help children prepare for and achieve goals, reduce anxiety and offer rewards when effective behavior has occurred [23]. More recent studies conducted in the United States have shown that the PAX version of the game reduces hyperactivity, increases prosocial behavior, improves children's academic skills and promotes teacher's self-efficacy [24], [25], [26].

The aim of this paper is to present the research protocol for the study designed to evaluate the impact of PAX GBG on students' mental health and behavior as well as teacher's self-efficacy in Estonia compared with the waiting list control condition. The newer version of the intervention (PAX GBG) has only been experimentally evaluated in English-language environments. Amendments were made on surface level (adapting language and images) and the underlying logic of the program was preserved during the adaptation in Estonia. At the same time, the adaptation to a new country and language, as along with the novel socioeconomic, educational and cultural environment, could feature prominently with regards to the effectiveness of the intervention [27].

## Methods/design

2

### Design

2.1

This study is an ongoing pragmatic, two-year, cluster-randomized waitlist-controlled trial conducted during school years, 2016/17 and 2017/18, in Estonia. One first grade class from each school among 42 schools participates in the study. Fig. 1 outlines the participant flow.

**Fig. 1 fig1:**
[figure not shown]
Participant flow.

### Study setting

2.2

The study setting is Estonian mainstream primary schools *(n*=*42).*

#### Inclusion criteria

2.2.1

Schools were suitable to participate if they had:-the Estonian language as the instruction language;-at least 13 pupils in the first grade class of the 2016/17 school year. A minimum cluster size was set to ensure enough pupils took part in the study and for better data monitoring;-a first grade teacher who volunteered to participate in the study over the course of its full period of two years.

#### Exclusion criteria

2.2.2

Schools were not suitable to participate if they:-were focused solely on children with special educational needs as the intervention has not been tested in schools for students with special needs in Estonia;-had the Russian language as the instruction language - the intervention has not been piloted yet with pupils from Russian-language classrooms;-had single-sex classrooms in first grade in order to balance gender within both arms of the trial;-implemented the ‘Kiusaamista Vastaan’ (KiVa) program, in order to reduce the risk of other evidence-based prevention programs affecting the results. KiVa is a bullying prevention program developed in Finland [28], that uses a whole school approach. As its components aim to affect skills, behavior, and classroom and school climate, it is assumed that it has a positive impact on children's social and emotional well-being, a primary outcome in this study.-implemented the PAX GBG (in one or several classes) so as to reduce the risk of contamination.

#### Participants

2.2.3

Participants are students from participating schools. In the 2016/2017 academic year the participants are first grade students (seven to eight years old) and in 2017/18 participants are in second grade (eight to nine years old).

### Recruitment

2.3

A list of all Estonian-language primary schools was obtained from the education database, EHIS, administered by the Ministry of Education in the spring of 2016. Schools that had at least 10 first grade students per class in 2015/16 were selected to be contacted as the class sizes in 2016/17 were not known yet.

Invitations to take part in the study were sent in the spring of 2016 to 164 schools, which fit with the inclusion criteria. Invitation forms included a brief introduction of the program, the conditions of participation and a description of the goal and procedures of the study. If a school was interested in participating, the representative from the school signed the request form and wrote the name of the volunteering first grade teacher. By signing the form, the school conveyed that they understand the conditions for participation (e.g., the random assignment of schools to the intervention and control arms of the trial, willingness not to sign up for the KiVa program during the study period, agreement to participate in the intervention-related activities).

The incentives for schools to participate in the study were PAX GBG materials, participation in a three-day PAX GBG training and mentoring support for the teacher for one year.

55 schools sent back the interest form. Six of them withdrew their participation by the summer. Reasons for withdrawal were changes with personnel and lack of time. Three schools did not meet the eligibility criteria (not enough students or Russian as an instruction language) and were excluded, leaving 46 schools for the trial. All withdrawals and exclusions happened before randomization.

### Randomization

2.4

46 schools were matched to pairs by geographical location and class size. Matching was used to facilitate implementation all over Estonia. There are 15 regions in Estonia, 11 have a local trained PAX GBG mentor. To ensure regional coverage of schools implementing the intervention (which is a regulation set by the funder) and to provide mentors with work within reasonable distance, matching was decided as the best option for achieving the research- and implementation-related goals.

Blocking or stratification is usually used in randomized experiments to improve precision [29]. In addition to accomplishing implementation-related goals, pairing (two schools per block) is expected to reduce intervention and control group differences at baseline and increase the statistical power. However, matched randomization also has several weaknesses [30] that will be taken into account within the study (i.e. if a school exits the trial after enrollment, the paired school will also be dropped; analytical limitations).

After matching, pairs were randomized into two groups. One school from each pair was randomly selected to receive the PAX GBG or to continue their activities without receiving the intervention (business as usual/BAU). The intervention is targeted at Year 1 students and hence one of the 1st classes was selected randomly from each of the participating schools (if there was more than one 1st grade).

Cluster randomization was conducted in September 2016 by an independent statistician from the Estonian-Swedish Mental Health and Suicidology Institute (ERSI). A random number generator, which employs atmospheric noise to generate truly random numbers, was utilized [31].

Following randomization and baseline data collection, the schools were contacted by phone and the results of the randomization were explained. Two schools from the intervention group dropped out after the randomization and hence their matched pairs in the control group were also removed from the study. One school wanted the third grade to participate (instead of the first) and the other was not able to ensure it was possible for the teacher to participate in the PAX GBG trainings.

### Minimum detectable effect size

2.5

A calculation was carried out to estimate the effect size the trial could detect as statistically significant. Cohen's d was used as an effect size measure. As an outcome variable, the *Teacher-Rated Strengths and Difficulties Questionnaire* (SDQ) total difficulties score at first post-assessment was considered.

For calculating the minimum detectable effect size (MDES) we considered two scenarios. For the first, we took into account the matched-pair design. However, as our matching criteria had presumably only weak associations with the outcome variable, the MDES calculations were also performed using simple cluster random assignment. In both cases, we used a significance level of 0.05 and a power value 0.8; average class size was an estimated 20 children. For the first scenario an intra-cluster correlation coefficient (ICC) of 0.15 was assumed for children in the same pair of schools. The effects of the pairs of schools were treated as random - with random intercepts and random effects on intervention. To account for intervention effect heterogeneity values of 0.5 and 0.75 were employed as a ratio of the variance of the intervention effect between pairs to the variance between pairs. On these conditions, 21 pairs with one intervention and one control school resulted in a MDES of 0.257 (or 0.286 if the random effects variance ratio was 0.75). Adding covariates to the children level (i.e. gender and baseline score) with an assumption of 20% variance reduction decreased the MDES value to 0.243 or 0.273.

With the second scenario, we discarded the level of pairs and assumed an ICC of 0.15 for children in the same school. The ICC for the primary outcome measure was based on earlier research in the field [32], [33]. The effects of the schools were considered as random intercepts. With 42 schools randomized to the intervention or control groups on a 1:1 bases, this scenario resulted in a MDES equal to 0.389. Again, adding children-level covariates (assuming a 20% variance reduction) diminished the MDES, yielding 0.380.

In other school-based intervention trials, the effects on students' mental health and well-being were found to vary between small and moderate [34]. Previous trials of GBG have found the effects on students behavior also to vary between small and moderate [35], [36]. Based on the calculations, we are aware that statistical power is an issue with this trial and we might be able to detect moderate effects.

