### Limitations

3.1

Several methodological challenges influenced the design of this trial. First, cluster-RCTs require large sample sizes of participants to be able to detect small or moderate effects between the intervention and control group. It was thought to be impossible from the start of this study to involve large amounts of schools in this trial and, therefore, sample size calculations were not performed. There are altogether 472 schools in Estonia providing primary education in Estonian, of which most are small in size with an average of 10 students per classroom. Before the start of this trial, 79 schools were already implementing the KiVa or PAX GBG programs. As a consequence, it was possible to invite 164 schools to the trial, from which one-third showed interest after receiving several invitations.

Even though the number of schools participating in the trial was not large, the input from this study is important to guide policy-related decisions in Estonia as well as encourage similar study designs in other countries regardless of the limitations and challenges that may arise.

Secondly, the preliminary aim was to use a simple-cluster randomized design. Based on the implementation-related goals, the final decision was to perform a matched-cluster randomization trial instead, which has its own weaknesses. It is unknown whether the matching was effective as the variables matched are not expected to be correlated with the outcomes. Hence, it is difficult to predict whether matching has actually improved the power of the study or not.

Another issue involves the impact estimations, which will be based on mITT. The initial plan was to conduct an ITT analysis, the gold standard for assessing the superiority of the intervention in randomized trials [63]. Unfortunately, it was not possible to keep two schools in the study and thus their matched schools were also excluded. At this moment it is assumed that this did not increase the potential for bias.

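### The matched-pair MDES figures (0.257/0.286; 0.243/0.273 with covariates) carry no school-within-pair variance, so they hold for this design only if matching is strong, which the article does not expect

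*Protocol article*

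**What the plan says.** Section 2.5 of the protocol article gives two sensitivity calculations for the teacher-rated SDQ total difficulties score at the first post-test. For both, "we used a significance level of 0.05 and a power value 0.8; average class size was an estimated 20 children".

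- **Scenario 1 (matched pairs).** Here "an intra-cluster correlation coefficient (ICC) of 0.15 was assumed for children in the same pair of schools". The model is described as follows: "The effects of the pairs of schools were treated as random - with random intercepts and random effects on intervention". Heterogeneity enters as "a ratio of the variance of the intervention effect between pairs to the variance between pairs", set to 0.5 or 0.75. The result is that "21 pairs with one intervention and one control school resulted in a MDES of 0.257", or 0.286 at the larger ratio. A 20% child-level variance reduction gives 0.243 or 0.273.
- **Scenario 2 (pairs ignored).** The same 0.15 is now the ICC for children in one school. With 42 schools the MDES is 0.389, or 0.380 with covariates.

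Section 2.4 randomises schools within pairs. Section 2.10 plans a three-level model (child, school, pair) when the baseline correlation of paired school means is above 0.4, and otherwise breaks the pairs. On matching, section 2.5 says "our matching criteria had presumably only weak associations with the outcome variable", and section 3.1 says "the variables matched are not expected to be correlated with the outcomes".

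**The concern.** The randomised unit in scenario 1 is the school, so differences between the two schools of a pair are part of the error of every pair contrast. The description in section 2.5 lists a pair intercept and a pair-by-intervention effect but no school term, although the planned paired analysis has a school level. The same 0.15 serves as the pair ICC in one scenario and the school ICC in the other. Children in one school also share its pair, so equal values leave no school variance beyond the pair unless the heterogeneity term supplies it.

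At stake is the stated sensitivity of the analysis that becomes primary if matching proves effective. Read at face value, pairing cuts the MDES from 0.389 to 0.257, about a third, although the article itself doubts that the matching variables relate to the outcome.

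**Working it through.** **Inputs (section 2.5 unless noted).** Significance level 0.05 (two-sided; a one-sided test does not reproduce the figures), power 0.80, 20 children per class (40 per pair), 21 pairs, ICC 0.15, heterogeneity ratio w = 0.5 or 0.75, child-level R² = 0 or 0.20. The matching threshold of 0.4 comes from section 2.10. The within-pair correlation of school effects, r, is not given and is varied below.

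**Step 1: reproduce scenario 1.** With 20 df the multiplier is t(0.975) + t(0.80) = 2.946. The two-level formula for children randomised within blocks is

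MDES = 2.946 × √[0.15w/21 + 0.85(1 − R²)/(0.25 × 21 × 40)]

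- w = 0.5, R² = 0: 2.946 × √(0.003571 + 0.004048) = 0.2571
- w = 0.75, R² = 0: 2.946 × √(0.005357 + 0.004048) = 0.2857
- w = 0.5, R² = 0.2: 2.946 × √(0.003571 + 0.003238) = 0.2431
- w = 0.75, R² = 0.2: 2.946 × √(0.005357 + 0.003238) = 0.2731

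All four printed values match. Normal quantiles, a one-sided test, or 20 children per pair do not match.

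**Step 2: reproduce scenario 2.** With 40 df the multiplier is 2.872. Then 2.872 × √[2(0.15 + 0.85(1 − R²)/20)/21] = 0.3888 (R² = 0) and 0.3802 (R² = 0.2). Both match.

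**Step 3: the matched-pair cluster formula.** With one school of 20 per arm in each pair and school ICC 0.15,

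MDES = 2.946 × √{[2 × 0.15(1 − r) + h + 2 × 0.85(1 − R²)/20]/21}

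where h is any genuine variation of the effect between pairs. The child term equals that of Step 1 (0.085 per pair when R² = 0). The only difference is that Step 1 has 0.15w where this formula has 0.30(1 − r) + h.

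**Step 4: what the printed figures imply.** Set h = 0, so that the whole heterogeneity term counts as school variance.

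- w = 0.5: 0.30(1 − r) = 0.075, so r = 0.75
- w = 0.75: 0.30(1 − r) = 0.1125, so r = 0.625

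The variance of an observed school mean is 0.15 + 0.85/20 = 0.1925. On the scale of observed means the correlations are 0.15 × 0.75/0.1925 = 0.58 and 0.15 × 0.625/0.1925 = 0.49.

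**Step 5: MDES with the school term (school ICC 0.15, 20 df, h = 0).**

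| Within-pair correlation | R² = 0 | R² = 0.2 |
|---|---|---|
| 0 | 0.399 | 0.390 |
| 0.4, true school effects | 0.331 | 0.320 |
| 0.4, observed means | 0.309 | 0.302 |

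For the third row, 2.946 × √[2 × 0.1925 × 0.6/21] = 0.309. The 0.302 takes 0.4 as the correlation of the covariate-adjusted means. Holding instead the implied true correlation, 0.4 × 0.1925/0.15 = 0.513, gives 0.297. Both are about 0.30.

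**Step 6: power without covariates (noncentral t, 20 df).** At d = 0.257, power is 64% for an observed-mean correlation of 0.4, 59% for a true correlation of 0.4, and 44% for no correlation. At d = 0.286 with an observed-mean correlation of 0.4 it is 74%.

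**Step 7: added heterogeneity.** With h = 0.075 or 0.1125 (the article's ratios times 0.15) and R² = 0, the MDES becomes 0.356 or 0.377 at an observed-mean correlation of 0.4, and 0.436 or 0.453 at r = 0.

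**The case against.** The best defence is that the figures follow from their stated inputs. With one school per arm per pair, school variance within a pair and variation of the effect between pairs cannot be separated, so one term may stand for both. This is correct as algebra, and it is why the point is conditional. It does not rescue the figures, because the article presents the term as effect heterogeneity and the correlations it would imply conflict with what sections 2.5 and 3.1 say about matching. Section 2.4 does expect pairing to increase power, and section 3.1 calls its success unknown, but neither supports correlations of this size.

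A second defence is that section 2.10 uses the paired model only above 0.4, a threshold on observed means, and the implied 0.58 and 0.49 lie above it. This stands in part. The printed values are attainable if matching turns out strong. At the threshold itself the shortfall is from 0.309 to 0.286 or 0.257.

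A reader might infer that the true MDES is simply 0.40 and power at 0.257 only 44%. The documents do not support that as a general statement: those values belong to ineffective matching, where the plan would normally switch to scenario 2, already printed correctly as 0.389/0.380. A reader might also infer that the article claims to detect small effects. It does not: section 2.5 concedes that power is an issue and that moderate effects might be detectable, and section 3.1 says no sample size calculation was done.

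**Conclusion.** The point holds in a conditional form. The four scenario-1 figures come from a formula without school-within-pair variance, and they describe this trial only if true school effects correlate at 0.75 or 0.63 within pairs, contrary to the article's own expectation. At the plan's 0.4 threshold on observed means the MDES is about 0.31 (about 0.30 with covariates). It is 0.33 (0.32) if 0.4 refers to true school effects, and about 0.40 (0.39) if matching does nothing.

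These values assume a school ICC of 0.15, 20 children per class, 20 df and no added effect heterogeneity; any real heterogeneity raises them. The within-pair correlation is an assumption, because the article gives none. The identification of the formula is firm, since all four figures match to three decimals. The scenario-2 figures are correct, and the article's conclusion that only moderate effects may be detectable agrees with them. The fault is a stated sensitivity that is too favourable under the article's own premise; it is not a fault in the number of schools.

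**What to change.** In section 2.5:

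- Restate scenario 1 with a between-school, within-pair variance term and an explicit within-pair correlation, saying whether it refers to true school effects or observed means. Show a range, for example about 0.31 at 0.4 on observed means, 0.33 at 0.4 on true effects and 0.40 at zero, with the covariate-adjusted values alongside.
- State separately any effect heterogeneity added on top, and its effect on the MDES.
- If 0.257/0.286 and 0.243/0.273 are kept, mark them as requiring strong matching, with the implied correlations given.
- Use 0.389/0.380 as the headline sensitivity, and interpret a null result against that or the restated paired value, whichever analysis is run.

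The cost is a text correction and a less favourable stated sensitivity. Sample size, randomisation, data collection and the planned models are unaffected.
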